## Abstract

**Background:**

Individuals claiming a disability benefit after long-term sickness absence, have to undergo medical disability assessments. These assessments, often carried out by specialized physicians, can be complicated by wrong expectations or defensive attitudes of disability benefit claimants. It is hypothesized that empowerment of these claimants will enhance the physician-patient relationship by shifting claimants from a passive role to a more active and constructive role during disability assessments. Furthermore, empowerment of claimants may lead to a more realistic expectation and acceptance of the assessment outcome among claimants and may lead to a more accurate assessment by the physician.

**Methods/Design:**

In a two-armed randomized controlled trial (RCT), 230 claimants will be randomized to either the intervention or control group. For the intervention group, an interactive website was designed http://www.wiagesprek.nl using an Intervention Mapping procedure. This website was tested during a pilot study among 51 claimants. The final version of the website consists of five interactive modules, in which claimants will be prepared and empowered step-by-step, prior to their upcoming disability assessment. Other website components are a forum, a personal health record, a personal diary, and information on disability assessment procedures, return to work, and coping with disease and work disability. Subjects from the control group will be directed to a website with commonly available information only.

Approximately two weeks prior to their disability assessment, disability claimants will be recruited through the Dutch Workers Insurance Authority (UWV). Outcomes will be assessed at five occasions: directly after recruitment (baseline), prior to disability assessment, directly after disability assessment as well as 6 and 16 weeks after the assessment. The study's primary outcome is empowerment, measured with the Vrijbaan questionnaire. Secondary outcomes include claimants' satisfaction, perceived justice, coping strategy, and knowledge. A process evaluation will also be conducted.

**Discussion:**

This study evaluates the effectiveness of an interactive website aimed at empowerment of disability claimants. It is hypothesized that by increasing empowerment, the physician-patient relationship may be enhanced and claimants' satisfaction and perceived justice can be improved. Results are expected in 2010.

**Trial registration:**

NTR-1414

## Background

Physician-patient communication is one of the most important tools in health care, and is considered to be an essential aspect of high quality care [1,2]. Research has suggested that effective communication by physicians influences the rate of patient recovery, effective pain control, adherence to treatment regimens, and psychological functioning [2-4]. In order to optimize physician-patient communication, the last decades an extensive amount of studies have been conducted in which interventions were aimed at the physician's role. These interventions consisted mainly of different forms of communication skills training [5,6], and some other methods, such as giving physicians feedback about patient-based surveys [7].

Additionally, research on physician-patient communication has focused on increasing the patients' role in care provision as an important new approach to the improvement of health care [8,9]. The case for patient involvement is based on evidence that patients' active participation during the medical interview is associated with better health outcomes [10,11] and increased involvement improves aspects of medical care [12,13]. Patient-focused interventions to improve physician-patient communication consist of e.g.: information provision [14], helping patients to formulate questions to ask their physicians [15,16], and role-playing exercises that increase attention of behavioural styles [17]. Most of these interventions are based on an empowerment (patient 'activation') approach.

Patient empowerment is defined as *helping the patient to discover and develop the inherent capacity to be responsible for one's own life *[18] and is characterized by a sense of perceived control, self-determination and goal internalization [19,20]. It combines personal efficacy and competence, a sense of mastery and control, and a process of participation to influence decisions and institutions [21]. Previous studies have shown that empowering patients can be effective in improving the physician-patient relationship in primary care [16,22-24]. In the trial described in this article, we introduce patient empowerment into a whole new field of care: insurance medicine.

Through social insurance, workers can claim compensation when they are losing (part of) their income due to disability. To judge these disability benefit claims, disability assessments are carried out by specialized physicians. In these disability assessments, physicians have to make judgments regarding the claimants' medical status and his or her functional capacities concerning vocational rehabilitation [25]. In the Netherlands, these assessments are performed by social insurance physicians who work for the Dutch Workers Insurance Authority (UWV). Worldwide, physicians are involved in similar assessments, even though national practices may vary considerably under social insurance or disability legislation [26].

The way of assessing workers' disability by (insurance) physicians remains a topic of interest and discussion [27-29]. One of the main problems in adequately evaluating disability claims lies in the physician-claimant interaction [30]. Compared to the 'normal' physician-patient relationship, where a physician has a caring and therapeutic role, this specific physician-claimant relationship is complicated by the fact that insurance physicians have to engage in different kinds of roles (sometimes roles they are not used to): i.e. being a source of information; advocate and counselor; and adjudicator and certifier [31]. Consequently, many physicians report feeling uncomfortable with performing disability assessments [32].

On the claimant side, it often has been stated that a passive and defensive attitude during disability assessments causes strain in the physician-claimant relation. This claimant behaviour can be attributed to three factors.

First, social security arrangements often stimulate passive and defensive behaviour. The fact that claimants have to prove that they are ill (in order to receive a disability pension) causes problems in the assessment of disability and discourages claimants to return to work [33,34].

Second, it has been stated that disability claimants are often characterized as being passive because of the perception that their capacity is limited and their odds of returning to work is low [35]. This behavioural characteristic frequently has a greater influence on the duration of recovery than health-related factors such as the severity of the disability [36]. In the disability assessment, this often leads to discrepancies in views between the physician and the claimant on the claimants functional capacity.

Third, complicated and not fully transparent disability assessment procedures and social security arrangements cause a lack of claimants' knowledge and understanding about this topic and results in claimants frequently having wrong expectations of disability assessment outcomes. From this perspective, patient empowerment is expected to influence the process of disability assessment in a beneficial way.

As a consequence of the complicated relationship between physicians and claimants, many claimants experience disability assessments as injustice [30,37] and reports indicate that patient satisfaction with insurance physicians is lower than, for example, occupational physicians [38].

In an attempt to improve the insurance physician-claimant interaction, the present study aims at empowering claimants prior to their disability assessment. Patient (or claimant) empowerment is expected to strengthen the sense of control among the claimant, so that more directed information concerning his or her disability can be shared with the physician. This, in turn, can lead to a better relationship between physicians and claimants. The classical physician-patient relationship, where the interaction is dominated by the insurance physician, can make room for a more collaborative relationship: the so-called "physician-patient partnership" [39]. Additionally, empowerment of claimants may also lead to a shift in claimants' perception of their limitations, and in a more positive attitude towards return to work.

Because the Internet has a profound impact on health care and has the potential to empower and educate patients effectively, to support decision making, and to enhance the interaction between health consumers and professionals [40,41], the purpose of this study is to empower patients through an interactive website intervention. Next to existing evidence on the effectiveness of eHealth interventions [42], the Internet has the possibility to deliver information to a large audience easily and at a low cost. This will improve the chances of implementation of this pragmatic intervention.

In this article, we describe the design of a randomized controlled trial (RCT) of which the aim is to evaluate the effectiveness of an interactive website designed to increase empowerment of disability claimants. It is hypothesized that this website intervention will:

1. Increase empowerment among disability claimants.

2. Enhance the physician-patient relationship, so that both are more satisfied with the interaction during disability assessment.

## Methods/Design

The project *Empowerment *is a randomized controlled trial with four months of follow-up. Randomization will take place to two groups: an intervention group using an interactive website and a control group using a website with commonly available information only. The recruitment and data collection for this study started in January 2009.

The study design and procedures were approved by the Medical Ethics Committee of the VU University Medical Center (under number 08/194).

### Study population

Participants are claimants for a disability pension according to the Dutch *Work and Income Act (WIA)*, which can be claimed after being sick-listed for 104 weeks. All disability claimants will be recruited in three different offices of the Dutch Workers Insurance Authority, UWV (Leiden, Den Haag, Rotterdam). UWV is responsible for evaluating disability claims in the Netherlands. Claimants will receive an invitational letter for the disability assessment including a study information brochure. The latter will direct claimants to an online application form. This application form includes questions concerning the study's in- and exclusion criteria and an informed consent. Recruitment will take place over a 8-month period (January 2009 – August 2009).

All insurance physicians from the participating UWV offices, and responsible for disability assessments concerning the Dutch *Work and Income Act (WIA)*, were asked to participate in the study.

### Inclusion & exclusion criteria

For claimants, inclusion criteria of the study are:

1) Adequate knowledge of the Dutch language,

2) Having an email address.

Claimants will be excluded if they had had any disability claim assessment in the past.

### Sample size

A power analysis has been carried out for the main outcome measure, i.e. empowerment. Empowerment will be measured using the "VrijBaan" questionnaire [43]. This questionnaire consists of six subscales. Based on previous findings the expected standard deviation (SD) for each of these scales is 0.70 [43]. Power calculations indicate that, to detect a 10% difference in empowerment, 86 subjects are necessary in each study group (assuming that power = 0.90 and α = 0.05). Taking into account a drop out rate of 25%, a sample size of approximately 230 claimants will be required.

### Randomization

Randomization will be conducted at the individual claimant level. After baseline measurements, disability claimants will be randomized in either the intervention or control group. Randomization to these two groups will be done by block randomization. To prevent unequal groups, 3 blocks will be created (3 UWV offices). A computerized random number generator will draw up an allocation schedule for each block. In consequence of the nature of the intervention (interactive website vs. a 'sham' website with commonly available information), claimants will be blinded for study design. Insurance physicians will be aware of the study's design, but will not be informed about the allocation of disability claimants.

### Development of the intervention

To determine the specific content of the website, the process of Intervention Mapping was used as a supportive tool [44]. The following steps were taken:

#### Step 1: needs assessment

In May 2007 we started with a needs assessment. In this step we performed semi-structured interviews with 8 insurance physicians and two labour experts. During these interviews we asked these stakeholders what problems they encounter with claimants during disability assessments and what their needs were in their interaction with claimants.

Furthermore, we conducted a survey that was returned by 41 disability claimants who had had a disability assessment in the preceding month. In this survey we asked claimants how they had prepared for their disability assessment, what problems they had experienced and what suggestions or needs they had for the intervention.

#### Step 2: defining objectives

On basis of the needs assessment, we defined the intervention and learning objectives. These were to:

- Increase claimants' knowledge about social security arrangements and disability assessment procedures.

- Provide claimants with realistic expectations on disability assessment outcomes.

- Increase claimants' skills and self-efficacy to actively participate during their disability assessment.

- Give claimants the opportunity to interact with other claimants in order to increase social support.

- Increase claimants self-awareness on their functional possibilities and limitations, so that they are able to communicate this better with their physician.

- Increase 'general' empowerment of claimants by, for example, giving information and advice on how to cope with disease and work disability.

#### Step 3: systematic review

Next, we performed a systematic review in which studies that were aimed at increasing empowerment through online tools were retrieved. Interventions that were found to be successful in increasing patient empowerment were well studied in order to obtain insight into the effective elements. For example, we used synchronized audio and text fragments supported by video (so-called 'modules'), comparable to a study by Warmerdam et al. [45].

In step 3 we also contacted patient organisations experienced in issues around disability assessments and asked them for methods suitable for the intervention. Existing brochures and websites that contain information on how to prepare for a disability assessment were consulted for inspiration as well.

#### Step 4: focus groups

Based on the previous steps, a first concept of the intervention was developed. With this concept in mind, we held two focus groups in which we discussed the intervention with a group of six insurance physicians and a group of five claimants and representatives of patient organizations respectively. With feedback and input from the focus groups the concept was further developed. Some ideas for the intervention were omitted when support was lacking.

#### Step 5: website development

In September 2008 the beta version of the website http://www.wiagesprek.nl was launched online. In the following four months the site was beta tested by professionals and a representative of a patient organization. Additionally, we conducted a pilot study in this period among 51 claimants. On basis of obtained feedback from the professionals as well as the results of an evaluation form filled out by 30 of these 51 claimants we adapted the website into a final version.

### Description of the intervention

The final web-based intervention http://www.wiagesprek.nl will consist of several components:

First, the website will contain general information and features concerning absenteeism from work, including:

- Social security law arrangements, with simple explanations of the WIA and its procedures

- Disability assessment procedures, including detailed advice on how to prepare for a disability assessment

- Return to work information (e.g. information on how to approach rehabilitation offices)

- Information about patient organizations

- Personal experiences of people who underwent WIA procedures

- Coping with disease and work disability

- Links to other related websites.

Second, the site will contain an extensive forum that gives participants the ability to interact with other claimants who are in the same situation. This interaction could be about, for example, issues concerning their disability assessment or coping with disease and work disability. Information on the forum will be updated by a moderator, who will also answer questions on the discussion forum posted by participants.

Third, participants will be asked to complete five interactive lessons or 'modules'. Each module will prepare participants step-by-step for their consultation visit with the insurance physician of UWV. Participants will be able to finish the modules in their own pace in a period of approximately two weeks prior to their disability assessment.

In *module 1 *(~20 min), Dutch legislation procedures will be explained to subjects in order to increase subjects' knowledge about WIA procedures and the exact content of disability assessment. An interactive quiz will test subjects' knowledge at the end of the module.

*Module 2 *(~20 min) focuses on the consultation visit with the insurance physician of UWV. Subjects will be asked to fill out their medical record and keep up an online diary that will prepare them for the actual disability assessment.

In *module 3 *(~15 min), videos of patient-physician interaction will be shown to subjects in order to teach them how to actively participate during their consultation visit with the insurance physician.

In *module 4 *(~15 min), expectations of subjects' disability claim outcomes will be discussed. Also, an interactive tool (the "WIA meter") will help subjects to increase their self-awareness and will test their motivation to return to work.

*Module 5 *(~5 min) will summarize all previous modules and will discuss the 6 most important tips concerning preparation for the upcoming disability assessment.

Throughout the modules subjects will be asked to finish short assignments in order to increase motivation and self-awareness about their disease and situation.

See [Additional file 1] for screenshots of the website intervention.

### Study groups

All participants will be able to access the homepage of the website http://www.wiagesprek.nl. From this homepage, participants from the intervention group can enter the Internet intervention with a username and password. These will be sent to participants after they have filled out an online application form. Comparably, participants from the control group will be directed to a website with commonly available information only. This control group website will only contain brief information about disability assessment procedures, which can normally be found in standard UWV brochures.

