**Figure 1 F1:**
[figure not shown]
**Overview of study procedures**.

In the Dutch social security system, workers that are long term sick-listed can apply for a disability benefit at approximately 91 weeks after the start of their sick leave. Around the 102^nd ^week of being sick-listed, these workers will receive an invitation from UWV to visit an insurance physician,. Together with this standard invitation from UWV, this study will send along an invitational letter and the study's information brochure. In this brochure, instructions are given on how to participate in the study by filling out an online application form. This online form includes questions concerning the study's in- and exclusion criteria and an informed consent. Subjects who meet all the criteria and are willing to participate in the research will be directed to the baseline questionnaire (T_0_). When subjects finish filling out the baseline questionnaire, they will be randomized in either the intervention group or control group. Disability claimants who are randomized into the intervention group, will receive an email with a username and password that gives them full access to the website intervention. Participants who are randomized into the control group receive an email that directs them to a website with commonly available information only. Before each follow-up measurement, subjects from both groups will receive emails in which they are asked to fill out the online questionnaires. Reminders will be sent to increase compliance.

Insurance physicians receive a newsletter with information about the ongoing of the project. Directly after a disability assessment with a claimant participating in the study, insurance physicians will be asked to fill out a short questionnaire, which they will receive by email.

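### An intervention-only login on a homepage open to both arms puts the stated claimant blinding at risk for the claimant-rated outcomes, including empowerment

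*Protocol article*

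**What the plan says.** The protocol article, under Randomization, argues from the comparison of an interactive site with a sham site that "claimants will be blinded for study design". For physicians it makes a different statement: "Insurance physicians will be aware of the study's design, but will not be informed about the allocation of disability claimants".

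The Study groups section describes access. "All participants will be able to access the homepage of the website", at the address that Description of the intervention gives for the intervention itself. It continues: "From this homepage, participants from the intervention group can enter the Internet intervention with a username and password". Of the comparator it says: "This control group website will only contain brief information about disability assessment procedures, which can normally be found in standard UWV brochures".

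Study procedures describes what is sent after baseline and randomisation. Claimants allocated to the intervention "will receive an email with a username and password that gives them full access to the website intervention". For the other arm: "Participants who are randomized into the control group receive an email that directs them to a website with commonly available information only". It mentions no credentials for controls.

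**The concern.** A sham comparator protects blinding only while those who receive it have no cue that a fuller version exists. Here both arms can open the front page of the intervention site, and only one arm is said to be sent the means to go further. A control who visits that page could work out that there is a restricted programme and that they were not given it.

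This matters because claimants rate most of the outcomes themselves: empowerment, claimant satisfaction, perceived justice, subjective knowledge, expectations, coping strategy and perceived work ability. Several of these ask about control or fairness, and answers could shift if a claimant believes help was withheld before a high-stakes assessment. Dropout could also differ between the arms. Either effect would be read as an effect of the website's content.

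**Working it through.** **The access arrangement, side by side**

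| Point | Intervention arm | Control arm | Section |
|---|---|---|---|
| May open the intervention site's homepage | Yes | Yes | Study groups |
| Enters from that homepage with credentials | Yes | Not stated | Study groups |
| Content of the email after randomisation | Username and password | Direction to an information-only site | Study procedures |
| Content reached | Five modules, forum, diary and other components | Brief brochure-type information | Description of the intervention; Study groups |

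The first three rows together leave controls with access to the page but, as far as the text goes, no means of entry. The last row is a second possible cue, because the control content is thin.

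**Which outcomes are exposed**

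Baseline (T0) is completed before randomisation, so it cannot be affected. Empowerment is measured again at T1 (the Competence and Impact subscales) and at T4 (all subscales), both after access has been given. A shift at those times would therefore pass straight into the change from baseline that the primary analysis compares. Physician satisfaction is rated by physicians who are not told the allocation, and return to work comes from UWV data. Neither depends on claimant blinding.

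**The plan's own sample size**

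Inputs from Sample size: SD 0.70, power 0.90, α 0.05 (two-sided assumed), 86 per group, 25% dropout. The 10% difference is not given in points.

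- Assuming a difference of 0.35 (10% of an assumed mean of 3.5), the normal approximation gives 85 per group. The t-test gives 85.03, so 86. A difference of 0.30 would need 115 per group and 0.40 would need 65.
- Dropout: 172 / (1 − 0.25) = 229.3, so 230, as stated.
- Working back from 86 per group, the detectable effect is (1.960 + 1.2816) × √(2/86) = 0.494 SD, or 0.494 × 0.70 = 0.346 points.

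**Illustration of what a bias could do**

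The size of the bias, b, is assumed; the documents give none. With no true effect and n = 86 per group, a simple two-group comparison is shifted by b × √(n/2) = b × √43. The rejection probability is Φ(shift − 1.960) + Φ(−shift − 1.960).

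| Assumed b | In points (SD 0.70) | Shift | Two-sided rejection rate |
|---|---|---|---|
| 0 | 0 | 0 | 0.050 |
| 0.1 SD | 0.07 | 0.656 | 0.101 |
| 0.2 SD | 0.14 | 1.311 | 0.259 |

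These biases are about one fifth (0.1/0.494) and two fifths (0.2/0.494) of the detectable effect. Each b is an average over the whole control arm. If only half of the controls noticed, an average of 0.1 SD would require a shift of 0.2 SD in each of them. The planned repeated-measures analysis has a different standard error, so the rates indicate scale only.

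**The case against.** A reader might infer that controls are routed through the intervention homepage, see a locked programme and are shut out, so that blinding is undone. The documents do not support that reading.

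- **Route.** Controls are able to access the homepage, but Study procedures emails them to another website. Nothing says that they must pass through the homepage.
- **No login.** This is inferred from silence. Study groups says loosely that credentials go to participants after the application form, then describes the control route as comparable. Intervention-only credentials are the natural reading of the two sections together, but not an explicit statement.
- **What is visible.** The homepage is not described, and the figure and screenshots are not shown. A login field alone need not reveal a second trial arm.
- **The blinding claim.** It concerns study design, whereas the physicians' statement concerns allocation. Whether claimants stay unaware of the design depends largely on the information brochure, which is not shown.
- **Direction.** Disappointed controls might score lower, favouring the intervention. They might equally look for information elsewhere, which would pull towards no difference. Differential dropout has no determined direction either.
- **Scope.** The second hypothesis covers physician satisfaction as well, and that half is not claimant-rated.
- **Remedy.** A control with a login still reaches brief brochure content, so symmetrical entry cannot hide the contrast completely.

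All of this stands as a limit on the claim. It does not remove the tension: the article states that claimants are blinded and also describes an arrangement that works against it.

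**Conclusion.** The point holds as a risk. The stated access arrangement gives controls a plausible way to learn that a restricted programme exists, and so weakens the stated claimant blinding for empowerment and the other claimant-rated outcomes. That blinding actually fails, for all or most controls, is not shown. The direction and size of any bias are unknown. Under an assumed arm-level shift of 0.1 to 0.2 SD, 86 evaluable claimants per group and a two-sided test, the 0.05 error rate would become about 0.10 to 0.26. The conclusion rests on reading Study procedures as giving credentials to the intervention arm only, and on at least some controls opening the homepage. It is a cheap improvement worth making, and it does not invalidate the design.

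**What to change.** - **Make entry symmetrical.** Send both arms identically worded emails with a username and password, and let the login open the allocated site. Alternatively, use neutral separate addresses so that the control route never shows the intervention homepage.
- **Measure what claimants believe.** Add one perceived-allocation question to a remaining questionnaire. At the end of T4 it cannot influence any earlier answer.
- **Qualify the claim.** In Randomization, describe claimants as not reliably blinded. This is needed even with symmetrical entry, because the brief control content may still reveal allocation.

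The Methods/Design section says recruitment and data collection started in January 2009, so a change of access may reach later entrants only. The question and the rewording can still be adopted. The cost is a small change to the login and the randomisation email, a minor login step for controls and one extra question. No extra participants or measurement occasions are needed.
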